## Abstract

**Background:**

Indigenous Australian children and adolescents experience profound levels of preventable dental disease. The application of silver fluoride (AgF) to active dental caries is a noninvasive alternative to traditional dental treatment approaches. There is particular utility among Indigenous children and young people with dental fear, who may not have access to timely or culturally safe dental service provisions.

**Objective:**

The aims of this study are to: (1) assess levels of active dental caries among Indigenous children and young people in 6 Australian states and territories; (2) determine if an AgF intervention reduces levels of active disease over 12-24 months; (3) measure the impact of improved oral health on social and emotional well-being (SEWB) and oral health-related quality of life; and (4) calculate the cost-effectiveness of implementing such an initiative.

**Methods:**

The study will use a 2-arm, parallel cluster randomized controlled trial design. Approximately 1140 Indigenous children and youth aged between 2 and 18 years will be recruited. Each state or territory will have 2 clusters. The intervention group will receive the AgF intervention at the start of the study, with the delayed intervention group receiving the AgF intervention 12 months after study commencement. The primary outcome will be the arrest of active carious lesions, with arrested caries defined as nonpenetration by a dental probe. Secondary outcomes will include SEWB, oral health-related quality of life, and dental anxiety, with covariates including dental behaviors (brushing and dental visits). Effectiveness measures for the economic evaluation will include the number of children and young people managed in primary oral health care without the need for specialist referral, changes in SEWB, the numbers and types of treatments provided, and caries increments.

**Results:**

Participant recruitment will commence in May 2023. The first results are expected to be submitted for publication 1 year after a 24-month follow-up.

**Conclusions:**

Our findings have the potential to change the way in which active dental disease among Indigenous children and young people can be managed through the inclusion of specifically tailored AgF applications to improve dental health and SEWB delivered by Indigenous health care workers. Desired impacts include cost savings on expensive dental treatments; improved SEWB, nutrition, social, and learning outcomes; and improved quality of life for both children and young people and their caregivers and the broader Indigenous community. The AgF application could be easily implemented into the training program of Indigenous health workers and yield critical information in the management armamentarium of health and well-being recommendations for Australia’s First Peoples.

**International Registered Report Identifier (IRRID):**

PRR1-10.2196/48558

## Introduction

### Young Indigenous Australian Oral Health

Indigenous Australian children and adolescents experience profound levels of preventable dental disease [1]. These have an impact on Indigenous children’s and young people’s ability to eat, speak, socialize, and learn. It is a leading cause of child malnutrition, poor quality of life, and nonoptimal social and emotional well-being (SEWB) [2]. Trajectories of dental disease among Indigenous children and adolescents are increasing at a rate far greater than for non-Indigenous children and adolescents, with severe cases requiring care under a hospital-based general anesthetic [3]. Poor oral health in childhood is the leading cause of poor oral health in adulthood [4] and has associations with other systemic conditions, including diabetes, cardiovascular disease, and chronic kidney disease [5].

### Dental Treatment Under General Anesthesia

Provision of dental care to young children can pose many challenges because of their emotional and physical development and lack of cooperation in the dental chair. The issues are multiplied for Indigenous children in rural and remote locations, where access to dental care is severely limited. Hospital-based treatment under general anesthesia is becoming an increasingly used mode of dental care for Indigenous children, with Australian Institute of Health and Welfare statistics showing that the rate of Indigenous Australian child admissions for dental treatment is twice that of non-Indigenous children [6]. However, dental treatment under general anesthesia does not prevent the occurrence of new dental decay, with children frequently readmitted for hospital-based dental general anesthesia after initial treatment [7]. Recent reports also suggest that oral rehabilitation under general anesthesia does little to alleviate dental fear or change noncooperative behavior and may, in fact, heighten these characteristics [8,9]. Moreover, comprehensive dental care under general anesthesia is not without risk, including the potential for long-term adverse neurodevelopmental effects [10-12]. Dental general anesthetics are extremely expensive for the taxpayer, the Australian health care system, and the community more broadly, and require considerable time and financial investments from carers (to transport the child to the hospital, stay overnight, ensure fasting before the operation, etc). The estimated mean cost of dental general anesthetics for Indigenous children is substantially higher than the cost of care for non-Indigenous children [10]. Treatment and preventive approaches that can be undertaken in Indigenous primary care settings to reduce the number of Indigenous children undergoing dental general anesthetics are thus urgently required.

### Interventions to Improve Indigenous Children’s Oral Health

In the past decade, there have been 4 published interventions aimed at reducing the burden of dental caries among Indigenous Australian children. Slade and colleagues [13] conducted a cluster randomized controlled trial of a dental health program that included the application of fluoride varnish to the teeth of Indigenous children aged between 18 and 47 months and dental education in 30 remote communities in the Northern territory. Although the study team reported reduced experience of dental disease among the intervention group compared with the control group, overall levels of dental disease at 2-year follow-up were extremely high, with 94% of children having experienced caries. Jamieson et al [14] conducted an early childhood caries intervention among Indigenous children and their families in South Australia, commencing during pregnancy and when children were aged 6, 12, and 18 months old. The intervention comprised dental care during pregnancy, fluoride varnish application to the teeth of children, anticipatory guidance, and motivational interviewing. At 5-year follow-up, children in the immediate intervention group had significantly less decay than those in the delayed intervention group (who received intervention at ages 2 to 3 years), but 47% of children still had experience of dental disease (Jamieson et al [14]). Smith et al [15] tested the effectiveness of a dental education program among young Indigenous children and their families from 8 Aboriginal Community Controlled Health Organizations (ACCHOs) in New South Wales. They reported that children in the education program had fewer dental caries at age 30 months than a comparator group drawn from the community, but the study did not follow standard randomization processes, meaning the conclusions are weakened (Smith et al [15]). Roberts-Thomson et al [16] used a silver fluoride (AgF) intervention among remote-dwelling Indigenous children and reported that children exposed to the intervention had less dental pain, dental extractions, use of antibiotics for dental infections, and fillings than children not exposed to the intervention. AgF was reportedly well accepted, easy to use, and at least as effective as conventional dental care (fillings and extractions). There were limitations, however, including a lack of robust randomization, only 2 trial sites included, only primary molar teeth included, a large loss to follow-up, and outcome measures not including specific assessments of dental caries or any patient-reported outcome measures such as oral health-related quality of life (OHRQoL), SEWB, and dental anxiety. As such, it has not been able to influence policy. A study that has more rigor (ie, is properly randomized), has a larger number of study sites (ie, more power in a statistical sense), uses explicit measures of dental caries (such as tooth surfaces with active dental decay), includes all present teeth, and comprehensively measures changes to SEWB, quality of life, and anxiety is urgently needed. Only then can we realistically expect policy changes, with the ultimate goal being to introduce the treatment for adults as well.

### What is Silver Fluoride and How Does it Prevent Dental Caries?

AgF is a cariostatic agent clinically applied to manage active dental caries to prevent further progression of disease. The fluid comprises 2 key therapeutic ingredients: silver and fluoride. The fluoride helps replenish the fluoride reservoir in the enamel (the outermost surface of the tooth) to ensure a robust crystalline structure and to promote the remineralization of carious lesions. Formulations of AgF at 38% present the highest concentration of fluoride (44,800 ppm F) among the available remineralizing agents—nearly twice the concentration of professionally applied fluoride varnish (22,600 ppm F) [17]. The silver acts as an antimicrobial agent, altering the composition of cariogenic biofilm within the dentine tubules of treated lesions (Sulyanto et al [18]). In contact with decalcified dentine, AgF forms insoluble silver microwires that block dentine tubules and contribute to the increased hardness of tissues [19]. AgF also has an inhibitory effect on matrix metalloproteinases involved in the degradation of collagen [20]. Unlike other modes of treatment for active dental caries, AgF may be applied by nondentally qualified staff, meaning the cost-benefit ratio is substantial [21]. Although it has been around for at least fifty years, the uptake of AgF has been limited because, under the old formulation, the active ingredient (silver) stained decalcified soft dentine black. However, the application of a potassium iodide solution immediately after the placement of AgF has been reported to reduce staining and improve aesthetic outcomes [22,23]. The World Health Organization has recently included AgF on the list of essential medicines for children [24].

### Why is Economic Evaluation Important?

In Australia, the Pharmaceutical Benefit Advisory Committee and Medical Services Advisory Committee require evidence of cost effectiveness for their reimbursement decisions. As such, it is important to conduct an economic evaluation for any health intervention to ensure financial sustainability in addition to clinical effectiveness. Moreover, to convince state and federal health services to sustain the funding of a new health intervention, it is imperative to prove the cost-effectiveness of the program. In the broader scientific community, there is now an expectation that clinical trials evaluating medicines and procedures should additionally assess the economic value of such interventions [25]. This expectation reflects both interest in economic information for new technologies and the regulatory and reimbursement regimes that require evidence of economic value along with clinical efficacy before implementing policy change. Nowhere is this more critical than in the field of young Indigenous Australian dental care. Indigenous Australians experience a disproportionate burden of disease, which translates into a 30% higher cost of health care delivery per capita for Indigenous populations compared to the general population [26]. Any demonstration of the cost-effectiveness of a dental care intervention over standard care is going to be of benefit to not only Indigenous children receiving the intervention but also to taxpayers contributing to the health care budget. To the best of our knowledge, there have been few evaluations of the cost-effectiveness of child dental caries interventions. The only one within the Indigenous child dental space was evaluated by Kularatna et al [27], with economic evaluations of dental health interventions per se being scarce.

Most ACCHOs in regional and remote locations in Australia are unable to provide dental care, yet they recognize that these services are critically important [28]. AgF can be applied by nondental personnel in home environments with minimal cost and equipment. This means AgF implementation, uptake, and cultural acceptability are superior to many other expensive health service models delivered by non-Indigenous staff.

The aims of this study are to (1) assess levels of active dental caries among Indigenous children and young people in 6 Australian states and territories; (2) determine if an AgF intervention reduces levels of active disease over 12-24 months; (3) measure the impact of improved oral health on SEWB and OHRQoL; and (4) calculate the cost-effectiveness of implementing such an initiative.

## Methods

### Overview

This is an Indigenous-led project conducted in partnership with ACCHOs across 6 states or territories in Australia. Meaningful and respectful engagement with ACCHOs ensures Indigenous self-determination and culturally appropriate research practices for the context of each Indigenous community throughout all stages of the study.

### Study Design

The study will use a 2-arm, parallel, matched-paired cluster randomized controlled trial design with 2 study sites (clusters) in each partnering state and territory (Figure 1). The intervention group will receive the AgF intervention at the start of the study, with the delayed intervention group receiving the AgF intervention 12 months after study commencement.

**Figure 1 figure1:**
[figure not shown]
Study plan schema. AgF: silver fluoride; SEWB: social and emotional well-being.

### Inclusion Criteria

Indigenous children and young adults aged between 2 and 18 years with active carious lesions (nonpulpally involved) in the primary or permanent dentition residing in selected study clusters will be eligible. Caregivers or participants who are unable to provide written informed consent, participants with a history of allergy to silver, or those presenting oral ulceration will be excluded. At the tooth level, symptomatic or pulpally involved teeth (pulp exposure, presence of an abscess or fistula, obvious discoloration indicative of pulp necrosis, or premature hypermobility) will be excluded from receiving the intervention.

### Randomization

The randomization schedule will be developed by biostatisticians at the Australian Research Centre for Population Oral Health, who will not be involved in the trial, using a computer-generated block-randomized algorithm. The random allocation will be 1:1 per state and territory; that is, 1 cluster per state or territory will be randomly allocated as the intervention site, leaving the other cluster to be the delayed intervention site. Randomization will be done before baseline fieldwork. Field staff will have no access to the randomization algorithm, thus allowing the randomization process to be audited.

### Participant Recruitment

We will adopt recruitment strategies that have been successfully applied in our wide body of research with Indigenous communities across Australia and that build upon the extensive community consultation processes that have already been undertaken for the proposed study. We will employ local Indigenous people as research assistants to continue to facilitate community engagement and participant recruitment. These research assistants will, in turn, be guided by senior Indigenous project officers. All participants at baseline will receive a clinical dental examination by a calibrated dental examiner, with participants aged 15 years or older or caregivers asked to complete a baseline questionnaire containing items on SEWB, oral health-related quality of life, dental behaviors, and sociodemographic characteristics. Participants in the delayed intervention cluster will be able to access standard dental care during the first 12 months of the study at their own volition.

### Reimbursement for Time

As per our standard procedures for participants involved in health research projects, all participants will receive an Aus $20 (US $15) gift voucher as a reimbursement for their time at both the initial recruitment and 12- and 24-month follow-ups. Each participant will additionally receive a sample bag of oral and general health-related items at baseline, including fluoridated toothpaste and toothbrushes.

### Intervention

After cleaning teeth with dry gauze and drying the cavities with cotton pellets, dentally qualified research officers will apply 38% AgF (Riva Star Aqua Step 1, Southern Dental Industries Ltd) to sites of active caries in the primary and permanent dentition using a microbrush applicator and keeping the solution in contact with the lesion for 60 seconds. No attempts will be made to remove soft dentine. Potassium iodide (Riva Star Aqua Step 2, Sothern Dental Industries Ltd) will be applied immediately after Riva Star Aqua Step 1 until the white precipitate is clear, signaling that all free silver ions have reacted with the potassium iodide. Petroleum jelly will be applied to the lips and gingival mucosa to avoid direct contact of AgF with soft tissues. Participants will be instructed to refrain from drinking, eating, or rinsing their mouths for at least thirty minutes. A single AgF application will occur at the baseline visit for the immediate intervention clusters and at the 12-month follow-up for the delayed intervention clusters. Any participants requiring additional dental treatment at the baseline, 12-month, or 24-month follow-ups will be referred for standard dental care to the local dental service provider.

### Outcomes

The primary outcome will be the arrest of carious lesions in the dentition, with arrested caries defined as nonpenetration by a dental probe. Secondary outcomes will include SEWB, OHRQoL, dental anxiety, and dental behaviors. A SEWB measure has been developed by our team based on community consultation, item polling, and a theoretical framework that identified six core SEWB domains for Indigenous Australian youths: (1) feeling empowered; (2) feeling strong in my body; (3) feeling loved and safe; (4) feeling resilient; (5) feeling strong in my mind; and (6) feeling strong in my identity. OHRQoL will be assessed using the Caries Impacts and Experiences Questionnaire [29], which we have validated and successfully implemented in other studies involving Indigenous Australian children [30]. Dental anxiety will be assessed using the Child Dental Anxiety and Scale [31], modified to capture anxiety from adolescent participants, which we have also validated and implemented in studies involving Indigenous children [30]. Behaviors will be assessed using items from the 2012-2014 National Child Oral Health Survey [1]. These will include participant age when commenced tooth brushing, tooth brushing frequency, use of fluoride toothpaste, last time participant saw an oral health care provider, usual reason for participant to visit an oral health care provider, and consumption of sugar-sweetened beverages and foods.

Effectiveness measures for the economic evaluation will include the number of children and young people managed in primary oral health care without the need for specialist referral, changes in SEWB, the numbers and types of treatments provided, and caries increments. A cost-utility analysis will be undertaken using the recently developed dental caries utility index for adolescents [32] and ECOHIS-4D to measure the utility values of the health states experienced by children and young people [33].

### Oral Epidemiological Examinations

Caries experience will be collected through standardized oral epidemiological examinations by calibrated dental examiners. Didactic and clinical training for the examination teams will be conducted before baseline data collection, with refresher sessions provided during the fieldwork phase. Examinations will be in participants’ homes, ACCHOs, schools, or wherever the caregiver, child, or young person feels most comfortable. All examiners will be tested in the field against the senior trainer to estimate interexaminer reliability. Intraclass correlation coefficients for caries assessment scores will be used to assess reliability.

### Sample Size Calculation

Based on the literature, in which approximately 81% of carious lesions were estimated to have been arrested with AgF [34], the community intracluster correlation was calculated as 0.09. Using these parameters at 80% power, α=.05, and 12 clusters available (6 clusters per treatment arm), the estimated sample size required is 320 in each arm. Allowing for a 25% loss to follow-up each year, the estimated sample size is 570 per arm, or 95 children and adolescents per cluster (rounded up). Sample size estimations were undertaken on STATA 15 (StataCorp) using the commands for cluster randomized trials for proportions of caries arrest.

### Data Analysis

The trial has been registered in the Australian and New Zealand Clinical Trials Registry (ACTRN12622001066774p). All analysis will be reported according to CONSORT (Consolidated Standards of Reporting Trials) guidelines. Data analysis will use intention-to-treat approaches, with standard imputation measures used to manage missing data. The analysis plan for each aim is as follows.

Aim 1 (severity of dental disease in young Indigenous Australians): the severity of dental disease will be calculated using the decayed, missing, and filled tooth surface index (dmfs/DMFS) for the primary and permanent dentition. The 2014-2016 National Child Oral Health Survey will enable comparison with both general and Indigenous population-level estimates [1]. General analysis will comprise the chi-square and 1-tailed Student *t* tests within the study sample and a nonoverlapping 95% CI when comparing with population estimates.

Aim 2 (changes in dental disease following AgF intervention): the trial will be analyzed on an intention-to-treat basis according to group allocation. Generalized linear mixed models will be performed to determine differences in the primary outcome (arrest in dental caries) between the 2 groups and over time when the outcome is continuous. For binary outcomes, general estimating equations with the log binomial family will be used [35].

Aim 3 (economic evaluation of the intervention): the cost-effectiveness of the intervention will be estimated using standard approaches from a health provider perspective. Effectiveness measures will include quality of life and utility indicators. A literature review will inform long-term cost savings to the health system by improving Indigenous children’s and young people’s experiences of dental disease. The usual method of determining the cost effectiveness of a health intervention is by estimating the incremental cost effectiveness ratio, the ratio between the incremental cost and the incremental outcome. Incremental cost is the cost difference between the intervention and usual care, while incremental outcome is the outcome difference between the intervention and usual care. The economic evaluation will compare any incremental costs of the intervention (costs accrued in the intervention arm compared to those in the delayed intervention arm) to the full list of incremental primary and secondary outcome endpoints, all expressed in their natural units of measurement. Costs will be measured from activity data with pathway analysis to fully specify all activities in both the immediate and delayed intervention arms. Resource use will be obtained from research and provider records. Measured resource use will be valued using both existing estimates of the costs of each unit of resource use from market prices and the Medicare fee rates. Intervention costs will exclude research project costs. Standard discounting will be applied to both costs and outcomes, with uncertainty in these data subjected to sensitivity analyses.

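### Aim 1 compares dmfs/DMFS in children enrolled because they have active caries with population-level survey estimates, so the comparison is not like for like and would be expected to show worse disease

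*Protocol article*

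**What the plan says.** **Target.** The statement of aims at the end of the Introduction sets Aim 1 as to "assess levels of active dental caries among Indigenous children and young people in 6 Australian states and territories". It is not restricted to those who have disease.

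**Who is in the sample.** Under Inclusion Criteria, the people who can enrol are "Indigenous children and young adults aged between 2 and 18 years with active carious lesions (nonpulpally involved) in the primary or permanent dentition", living in the study clusters. Under Participant Recruitment, "All participants at baseline will receive a clinical dental examination by a calibrated dental examiner". No record is described for children who are screened and found to have no active lesion.

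**Measure and comparator.** Data Analysis, Aim 1, measures severity by decayed, missing and filled surfaces in both dentitions (dmfs/DMFS). It then says "The 2014-2016 National Child Oral Health Survey will enable comparison with both general and Indigenous population-level estimates", and gives as the decision rule "a nonoverlapping 95% CI when comparing with population estimates".

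**Caveats given.** Strengths and Limitations lists the evaluation of disease severity in Indigenous children and young people across six states and territories as the first strength. The limitations named are COVID-19, the lack of radiographs and the lack of participant blinding. Selection on active caries is not among them.

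**The concern.** A child without active decay cannot enter the trial sample but does contribute to a population estimate. Having the disease is the condition for being counted on one side of the comparison and not on the other. A difference in mean dmfs/DMFS would be expected even if the study communities had exactly the survey population's distribution of disease.

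Aim 1 is the first of four aims, and the article's conclusion says the study should add to understanding of Indigenous health at community level. A nonoverlapping interval would be read as evidence that these communities carry more disease than the Indigenous or general population, when eligibility alone could have produced it.

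**Working it through.** The article states no figure for this comparison, so there is none to reproduce. The check is algebraic, with assumed values where the article gives none.

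**Inputs from the article.** Eligibility requires active caries. The planned total is 1140, at 95 per cluster. The intracluster correlation is 0.09; it was given for the sample size on caries arrest and is borrowed here for dmfs/DMFS.

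**Assumed.** Population prevalence of active caries, p, from 20% to 90%.

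**Step 1: prevalence.** Every participant has an active lesion, so sample prevalence is 100% whatever p is. The sample carries no information on p.

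**Step 2: mean dmfs/DMFS.** Let μ1 be the mean in children with active decay and μ0 the mean in those without. The population mean is p·μ1 + (1 − p)·μ0. With k = μ0/μ1, and setting the pulpal exclusion aside, the ratio of sample mean to population mean is

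R = μ1 / [p·μ1 + (1 − p)·μ0] = 1 / [p + (1 − p)·k].

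If children without active decay have no missing or filled surfaces, k = 0 and R = 1/p, which is the upper bound. R exceeds 1 whenever k is below 1.

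**Step 3: allow for treated surfaces.** Assume a mean of 5 decayed surfaces in affected children. Assume also that 30% of all children, independently of active decay, have missing or filled surfaces, averaging 4 in those who have any. Then μ0 = 0.30 × 4 = 1.2, μ1 = 5 + 1.2 = 6.2, and the population mean is 5p + 1.2.

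**Step 4: allow for the pulpal exclusion.** Children whose only lesions are pulpally involved cannot enrol. As a rough stand-in, a simulation under the Step 3 assumptions removed the 10% of eligible children with the highest scores.

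| p | Upper bound 1/p | Population mean 5p + 1.2 | R = 6.2 / population mean | R after removing top 10% |
|---|---|---|---|---|
| 20% | 5.0 | 2.2 | 2.8 | 2.16 |
| 40% | 2.5 | 3.2 | 1.94 | 1.49 |
| 60% | 1.67 | 4.2 | 1.48 | 1.14 |
| 70% | 1.43 | 4.7 | 1.32 | 1.01 |
| 80% | 1.25 | 5.2 | 1.19 | 0.92 |
| 90% | 1.11 | 5.7 | 1.09 | 0.84 |

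**Step 5: the decision rule.** The design effect is 1 + (95 − 1) × 0.09 = 9.46, so the effective sample size is 1140/9.46 ≈ 120. In the simulation the standard error of the untrimmed sample mean was 0.51, giving a lower 95% limit of about 6.2 − 1.96 × 0.51 = 5.2 surfaces. The population mean lies well below this at p = 20%, 40% and 60% (2.2, 3.2 and 4.2). Unless the survey interval is wide, the rule would declare a difference there although none exists. At 80% the population mean (5.2) sits on the limit, and at 90% (5.7) it is inside the interval.

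**The case against.** The strongest reply has four parts.

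- **Direction.** A reader might infer that Aim 1 is guaranteed to overstate disease. The documents support that for prevalence of active caries, but the planned comparison is of dmfs/DMFS. For that mean the pulpal exclusion works the other way, and the last column of the table shows it can cancel or reverse the inflation at high prevalence. Treated surfaces in children without active decay also narrow the gap. This stands: overstatement is expected, not certain. The 10% trim is itself assumed, and children with a mixture of lesions remain eligible.
- **Size.** The Introduction cites caries experience of 47% and 94% in earlier studies of Indigenous children. These figures cover past as well as active disease, so they do not give p. They do leave open a high prevalence for the Indigenous comparator, where the inflation could be small. This stands too.
- **Choice of estimates.** The article does not say which survey estimates will be used, and age standardisation or choice of a subset may sit in an analysis plan not shown. That is fair for the detail. The comparator is nevertheless described as population-level, for both the general and the Indigenous population, and nothing restricts it to children with decay.
- **Measure.** It is tempting to add that dmfs/DMFS is the wrong index because the aim speaks of active caries. That goes too far: the index fits the label of severity used in Data Analysis, and it contains the decayed component. It is a reporting point only.

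None of this makes the stated comparison like for like.

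**Conclusion.** The point holds as a should-fix. As written, Aim 1 sets a sample selected on active caries against population-level estimates, and its decision rule could declare a difference that eligibility alone produced. The sample cannot estimate community levels of active caries. The expected inflation of mean dmfs/DMFS is at most 1/p, from 5.0 at a prevalence of 20% to 1.11 at 90%. It is smaller where children without active decay have treated surfaces, and its sign is uncertain at high prevalence because of the pulpal exclusion. These sizes rest on assumed prevalences and, beyond the 1/p bound, on assumed distributions. The conclusion also rests on the default reading that the survey estimates include children without active decay.

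A reader might also infer that Aim 1 has no value or that the trial is compromised. Neither follows. Severity among enrolled children can be described validly, and randomisation, the primary outcome, the sample size for caries arrest and the Aim 2 comparison do not depend on this analysis.

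**What to change.** Choose one of two changes to the Aim 1 text.

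1. **Restrict the comparator.** Compare only with survey children of the same age band who have untreated decay, and report the decayed (d/D) component alongside dmfs/DMFS. This needs subset or individual-level survey data, whose availability the article does not establish. State that a residual mismatch remains: the survey subset would include children with only pulpally involved lesions, who cannot enter the trial.
2. **Drop the comparison.** Remove the nonoverlapping-interval comparison with population estimates, restate Aim 1 as severity among children with active caries, and add the selection to the limitations. This is a wording change and needs no new data.

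The price of either is that the trial can no longer claim community-level disease levels from this sample.

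Recording dmfs/DMFS for children screened and found ineligible would help to recover community levels, but it is not free. Consent is described for participants only, several ethics committees have approved the study on that footing, and around 540 had been recruited by September 2023. Consent and ethics changes may be needed, and records not kept for children already screened could not be recovered.
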